### Study interventions

Both groups (IG and CG) will receive the standard conservative therapy comprising physiotherapy and drug-based pain management according to their individual needs. Additionally, the participants of the IG will receive MultiMove twice a week on non-consecutive days over a period of 12 weeks. The duration of each session is set to 60 min (see Table 1) with a successive progression in the level of difficulty over time (see Table 2). Each session consists of motor-cognitive, dancing and strength or flexibility exercises with reference to the current recommendations for physical activity in older adults provided by the American College of Sports Medicine [52].

**Table 1 Tab1:** Time slots for weekly training sessions (WTS) of 2 × 60 min in all phases

Training components	Phase 1–3	
	WTS 1* (Time)	WTS 2* (Time)
Life Kinetik® (including warm-up)	25 min	25 min
Dance	25 min	25 min
Strength	–	10 min
Flexibility	10 min	–

* ≥ 48 h rest between WTS

**Table 2 Tab2:** Details of MultiMove with exercise examples

Training components	Exercise	Examples of exercise Phase 1	Examples of exercise Phase 2	Examples of exercise Phase 3
		Week 1–4 │ Foundational	Week 5–8 │ Intermediate	Week 9–12 │ Advanced
Life Kinetik®	cognitive-motor exercises	balancing while counting backwards	bouncing a ball while solving arithmetic tasks	ball juggling and reacting to external stimuli
Dance	choreographies focusing on different dance styles	Line dance, Irish dance	Pasodoble, Salsa, Cha-cha-cha	Tango, Salsa
Strength	core stability and strengthening	pelvic tilt, abdominal hollowing	curl up, bridge, bird dog	side plank, hip abductor wall squat
Flexibility	range of motion through static stretching of core and hip muscles	knee to chest, piriformis stretch	hamstring stretch, hip flexor stretch, seated flexion	warrior one pose, warrior two pose

The classes will start with the motor-cognitive component, which includes a warm-up phase with movements for all major muscle groups. The following motor-cognitive exercises are in line with a licensed concept (Life Kinetik®, [32]). Here, motor and cognitive tasks have to be performed simultaneously, requiring a redistribution of attentional resources. The exercises are designed in a way that they can hardly be executed without mistakes and the difficulty level will be adapted to the ability of the participants. During the following dance part, the participants will learn choreographies with increasing complexity over time, which will be adapted to their disability level. The choreographies will include different dance styles (e.g. Latin, Standard, Jazz) whereby each style focuses on a specific aspect, e.g. spatial orientation in Line dance or posture in Latin dance. To ensure that on the one hand different performance levels do not influence the dancing, but on the other hand, participants interact socially, the choreographies will be performed individually in a group setting and will be supplemented by dance formations. The final strength and flexibility training will focus on evidence-based exercises for the spine, back, abdominal and hip muscles [53].

The sessions will be supervised by two accredited instructors and will be conducted with a maximum of 15 participants. Instructors will keep an attendance list at each class. If participants are absent for two consecutive intervention sessions, they will be contacted by telephone. In order to improve attendance to MultiMove, participants of the IG will be asked to visit at least 80% of the classes. Moreover, participants will receive global information about the purpose and usefulness of the intervention at the first training session as well as specific explanations during the respective exercises. The individual perceived enjoyment of MultiMove will be assessed via the German version of the Physical Activity Enjoyment Scale once a week [54].

Additionally, instructors will keep an activity log in each class to maintain intervention fidelity. Activity log will include a check-list with essential components of the intervention protocol and will be reviewed by an independent assessor. If participants will not be able to perform the planned exercises, because of the physical requirements, small individually adjusted modifications will be made and protocolled. Furthermore, if participants should premature terminate out of MultiMove, reasons will be recorded (e.g. personal reasons, relocation, illness that prevent physical activity or death).

The participants of the CG will be examined in the same time period as the IG receiving only the standard therapy (physiotherapy and drug-based pain management according to their individual needs), with the possibility to attend MultiMove as well, but not before the follow-up data collection is completed.

Besides, both groups will be asked not to start any (further) specific training intervention or pain treatment during the study period. Their physical activity level will be monitored by a questionnaire.

### Outcome measures

A detailed description of the outcome measurements is following, whereby Table 3 presents an overview of the addressed constructs with the assessment methods and respective parameters. Moreover, the measurement time points are marked in Table 3.

**Table 3 Tab3:** Constructs, assessment methods, parameters and data collection schedule

Constructs	Assessment methods	Parameters	Baseline (t0)	Post (t1)	Follow-up (t2)
Physical functions					
Mobility and function of the lower extremities	Timed Up-and-Go Test^1^	Time (s) to complete the task	X	X	X
Functional exercise capacity and dynamic postural control	Six-minute walk test with inertial measurement units (IMUs) and an electro-cardiogram	Walking distance (m) in 6 min, gait kinematics (e.g. minimum toe clearance, gait variability) and heart rate	X	X	X
Functional leg extensor muscle power	Five-repetition sit-to-stand test on a force plate	Time (s) and rate of force development	X	X	X
Flexibility	Instrumented trunk range of motion assessment	Active range of motion (°)	X	X	X
Subjective health state					
Back pain associated disability in daily life	Oswestry Disability Index	Total score (0–100%)	X	X	X
Health-related quality of life	EQ-5D-5L	Index value (−0.66 to 1) and subjective overall health state (0–100)	X	X	X
Motor-cognitive dual task performance					
Static and dynamic postural control during a cognitive challenge, haemodynamic response in the prefrontal cortex (PFC) and dual task costs	Single and dual task bipedal stance performance on a force plate (with and without closed eyes) as well as gait analysis with IMUs, functional near-infrared spectroscopy and finger oximeter	Deviation of the center of pressure (e.g. sway and velocity), gait kinematics (e.g. minimum toe clearance, gait variability, gait velocity), oxy- and deoxyhaemoglobin concentrations in the PFC, number of correct calculations and peripheral oxygenation	X	X	X
Executive functions					
Inhibitory control	Colour-Word-Interference Test	Time (s) and error rate	X	X	X
Cognitive flexibility	Trail Making Test	Time (s) and error rate	X	X	X
Psychosocial aspects					
Fear of movement	Tampa Scale of Kinesiophobia	Total score (11–44)	X	X	X
Pain coping strategies	Coping Strategies Questionnaire	Total score for each coping strategy (0–36)	X	X	X
Additional					
Sociodemographic data	Intake form	e.g. age, sex, education	X		
Physical characteristics	Intake form	e.g. height, weight	X	X	X
Current pain intensity	Numerical rating scale	Score (0–10)	X	X	X
Specific characteristic and treatment history of chronic pain	German Pain Questionnaire	Descriptive data, time period (months) of chronic pain, pain intensity (0–10) in the last 4 weeks	X	X	X
Level of everyday activity	Freiburger Questionnaire on Physical Activity	Time (h) of physical activity in a week	X	X	X
State fatigue	Fatigue subscale of the Profile of Mood States	Score (0–42)	X	X	X
Depression	Beck Depression Inventory II	Total score (0–63)	X	X	X

^1^Primary outcome measure; all instruments will be presented in German

### Primary outcome measure

#### Timed Up-and-Go Test

The TUG Test is commonly used in geriatric settings to assess function of the lower extremities, mobility and fall risk [55]. The patient will sit on a standard arm chair with his back and arms resting on it. A line will be marked on the floor 3 m away from the chair. At the command “go” the patient has to get up (without using the arms), walk as quickly and stable as possible to the marked line, turn 180°, return to the chair and get back into the starting position [55, 56]. To ensure, that the test procedure has been understood, the procedure can be tried once before the actual test. The time needed from releasing the back from the backrest to touching it again will be measured during the test. The TUG will be performed two times, whereby the fastest trial will be considered. It has been shown, that the TUG test can be performed reliably [55, 57].

### Secondary outcome measures

#### Physical functions

##### Six-minute walk test

The Six-minute walk test (6MWT) is an objective measurement to assess the functional exercise capacity close to activities of daily living by measuring the total walking distance accomplished in 6 min [58]. During the 6MWT, the participants will walk back and forth on a 15 m long track as fast as they can for 6 min. Additionally to the standard protocol, gait kinematics (e.g. minimum toe clearance (MTC) [59], double step length (DSL), gait velocity [60] and their variability) will be recorded, using three inertial measurement units (IMUs, one at each foot and one at the sternum, MTw, Xsens Technologies B.V., Netherlands). The calculation of gait parameters will be in line with the protocol of Hamacher et al. [59]. Furthermore, the participants will wear a portable 3-channel electrocardiogram with a finger oximeter (SOMNOtouch™ NIBP; SOMNOmedics GMbH Germany) to assess heart rate and peripheral oxygenation as an objective measurement of exercise intensity. Additionally, the subjective level of exhaustion [61] as well as the current pain situation on a NRS from 0 (not fatigued at all / no pain) to 10 (total fatigue & exhaustion / pain as bad as it could be) will be enquired before and after the 6MWT.

##### Five-repetition sit-to-stand test

The leg extensor muscle power will be assessed with the five-repetition sit-to-stand test (FRSTST) [62, 63] performed on a force plate (Type 9260AA, Kistler Group, Winterthur, Switzerland; sampling frequency: 1000 Hz). The participants will sit on a standard chair without armrest in front of a force plate. They will be asked to fold their arms across their chests, place their feet on the plate and to stand up and sit down as fast as possible five times in a row [62, 63]. During the performance, the investigator will ensure that the participants getting up fully upright and touch the surface of the seat completely. Participants are allowed to practice the process two times. The total time, from the starting signal to the fifth time seating, and the force-time curves, from which rate of force development can be derived, will be measured.

##### Instrumented trunk range of motion assessment

A sensor-based measuring device (mobbe®med, SportMed A.G. SA, Luxembourg) will be used to assess active trunk range of motion. Specifically, the participants will be asked to perform extension-flexion, lateral flexion (left and right) and rotation (left and right) of the spine. Thereby, the range of motion as well as the subjective pain sensation rated on a NRS (0–10) will be recorded.

#### Subjective health state

##### The Oswestry disability index

The ODI is a condition-specific, self-administered questionnaire for spinal disorders [64, 65]. It consists of 10 items, scored on a 6-point scale (0 to 5). One item assesses the extent of back pain, while the other nine ask for the difficulties in different activities of daily life because of the pain: personal care, lifting, walking, sitting, standing, sleeping, sex life, social life and travelling [66]. All items refer to the current (“today”) pain situation. The total score is multiplied by 2 and is presented as a percentage, whereby a higher score represents a higher level of disability [66]. In this study, the reliable and valid German version of the ODI will be used [66].

##### EQ-5D-5L

The EQ-5D-5L has been developed by the EuroQol Group and is an international, standardized, short questionnaire to assess generic health-related quality of life [67]. In the current study the German self-complete paper version will be used, which consists of two parts. The first part includes five items (health dimensions: mobility, self-care, usual activities, pain/discomfort and anxiety/depression). Here, each dimension can be scored on a 5-point scale (severity levels) corresponding to the problems the respondent has in this area (0 = no problem, 5 = extreme problems). The second part consists of a visual analogue scale (VAS) ranging from 0 to 100 (worst to best health the respondent can imagine), on which participants should indicate their current subjective overall health state. To calculate a EQ-5D-5L summary index score a country specific value set, which weights each level in each dimension specifically, will be used [68].

#### Motor-cognitive dual task performance

##### Single and dual task postural control performance with functional near-infrared spectroscopy and inertial measurement units

A portable functional near-infrared spectroscopy (fNIRS/NIRSport, NIRx Medical Technologies, NY, USA) and IMUs (described above) will be applied while performing postural control tasks with and without a cognitive task. Due to the fNIRS system requirements, the testing protocol has to alternate constantly between baseline (standing position with eyes open) and one of four action tasks. First two dynamic postural control tasks are conducted in random order: single task walking (STW) or dual task walking (DTW). Subsequently, two static postural control tasks - dual task standing (DTS) or closed eyes standing (CES) - are executed in a random order. For the dynamic conditions, the participants will have to walk a 15 m track back and forth with their individual comfort velocity. During static conditions, participants will stand as stable as possible on a force plate (Type 9260AA, Kistler Group, Winterthur, Switzerland; sampling frequency: 100 Hz) in an upright bipedal position with arms akimbo, looking straight ahead. The positions of the feet will be measured and noted, to ensure reliable measurements. In the dual task conditions, the participants will count backwards in steps of three from a pre-defined 3-digit number (between 300 and 400) while walking (DTW) or standing (DTS). Here, participants will be instructed to pay equal attention to both tasks. During the CES participants will be asked to close their eyes while continuing the stable stand.

Each action part will be assessed over a total of 2 min (split in four times 30 s) and the baseline over 2:45 min (five times 33 s). Hence, the total measuring time will be 4:45 min per task. In order to familiarize the participants with each task, a short version (10 s:10 s) will be performed once before actual testing. During all four tasks, the haemodynamic response in the PFC (relative oxy- and deoxyhaemoglobin concentrations) will be measured by a fNIRS system. Data recording, processing and analyses will be in line with the recently published guidelines for fNIRS in posture and gait research [69]. Additionally, gait kinematics (e.g. MTC, DSL, gait velocity and their variability) will be recorded with IMUs during the dynamic postural exercises. During the static tasks the deviation of the centre of pressure (e.g. sway and velocity) will be assessed based on the force plate data. The error rate and number of correct calculations of the cognitive task will be captured with a voice recorder. Furthermore, the participants will wear the SOMNOtouch (described above) to check for confounders in the haemodynamic response [70]. Here the outcome parameters are: heart rate, heart rate variability indices and peripheral finger oxygenation.

#### Executive functions

##### Colour-Word-Interference test

The Colour-Word-Interference Test (based on the Stroop effect [71]) is a frequently used neuropsychological test to assess inhibitory control [72, 73]. Here, the participants have to read out loud and as fast as possible nine tables. These tables consist of three different consecutive tasks that are presented three times: (i) read colour names (printed in black ink), (ii) name the colour of colour bars, (iii) name ink colour of colour names (printed colour never matches the written colour name) [71, 73]. The (iii) task is the incongruent condition requiring to inhibit the more automated task (e.g. reading the colour name), which is called the Stroop effect [71, 73]. The required time is stopped individually for each table and the corrected and uncorrected errors are determined for condition (iii). Additionally, the time difference between (ii) and (iii) is calculated [74]. In this study the German paper-pencil version of the Colour-Word-Interference Test will be used (Farbe-Wort-Interferenztest, [75]).

##### Trail Making Test (part A and B)

The Trail Making Test (TMT) is a neuropsychological test of visual search, processing speed and cognitive flexibility [76]. It consists of two tasks A and B, each requiring to connect 25 consecutive targets as quickly and accurately as possible. In part A, numbers (1–25) presented randomly on a piece of paper have to be connected in ascending order as fast as possible. Part B requires mental shifting between presented numbers (1–13) and letters (A-L). They have to be connected in alternating order (1, A, 2, B…). The processing time for each part will be recorded.

#### Psychosocial aspects

##### Tampa Scale of Kinesiophobia

The Tampa Scale of Kinesiophobia - German version (TSK-GV) is a valid and reliable 11-item self-report questionnaire measuring the fear of movement and reinjury [77]. Participants are asked to rate each item between one (strongly disagree) and four (strongly agree). Hence, a higher overall score represents a stronger individual’s fear of movement [77].

##### Coping Strategies Questionnaire

The Coping Strategies Questionnaire is a reliable measure for pain coping techniques [78]. In this study, the German version will be used (CSQ-D) [79]. The CSQ-D comprises 50 items in total. The first 48 items describe different cognitive or behavioural coping techniques (cognitive: diverting attention, reinterpreting pain sensations, coping self-statements, ignoring pain sensations, praying or hoping, catastrophizing; behavioural: increasing activity level, increasing pain behaviours). Participants are asked to rate how frequently they use each of the described coping techniques on a 7-point scale (0 = never, 6 = always). Additionally, two items assess their self-reported overall effectiveness of their strategies. To evaluate the CSQ-D, a score is calculated for each coping technique ranging from 0 to 36 [79].

### Additional measurements

Additionally, demographic (e.g. age, sex, education), physical characteristics (e.g. height, weight) and the current pain intensity on a NRS (0 - no pain to 10 - pain as bad as it could be) will be assessed. Moreover, information which could possibly influence the treatment outcome will be recorded. Hence, the specific characteristics and treatment history of chronic pain will be evaluated with parts of the German Pain Questionnaire [80, 81]. The level of everyday physical activity will be assessed with the Freiburger Questionnaire on Physical Activity, collecting self-assessed data to the amount of leisure and work related activity [82, 83]. The level of state fatigue and depressive symptoms at the measurement days will be estimated trough the fatigue subscale of the Profile of Mood States (POMS-F) [84] and the Beck Depression Inventory II (BDI-II) [85].

The participants will receive a medical check-up at the end of the study period at the same orthopaedic department where the initial check-up takes place, to recognize beneficial and adverse events related to the study intervention. Any other harms, occurring during the study intervention, will be protocolled by the accredited instructors.

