### Data analysis and management

Data will be analysed using IBM SPSS 26.0 (SPSS Inc., Chicago, IL). At first, a descriptive analysis will be conducted to identify outliers, distributions and to display the baseline characteristics of both groups (means, proportions, standard deviations). To evaluate the effects of the intervention, data of all patients will be processed, regardless of whether they fully received or dropped out of the intervention (intention-to-treat-analysis). Thereby, data will be analysed until the date of drop out. As a secondary analysis, only the data from the participants who participated at least 80% of the intervention will be included in a per-protocol analysis. Missing data will be imputed using multiple imputation, under the assumption that data are missing at random. Statistical significance level will be set at *p* ≤ 0.05 (1-sided).

In order to analyse differences between the groups at the time points post and follow-up, two ANCOVAs with baseline adjustments will be undertaken (covariates: baseline values and, when required, e.g. age, sex etc.) for all outcome measures. Subsequently, alpha-adjustments will be undertaken. In case the assumptions for the ANCOVA will be violated, mixed models will be used. To further elaborate the outcomes and their interactions, additional parametric or nonparametric statistical analyses will be applied. Exploratory mediation analysis will be performed supplementary.

To preserve the confidentiality, all participants will receive a specific code with which the data will be labelled, while the participants contact data will remain under lock. The collected data will be stored digitally and can only be accessed by the study group. Therefore, the data will be transmitted by one person and checked for correctness by another (transmission errors and plausibility). In this study, no data monitoring committee and interim analysis will be established, because of the minimal risks associated with the intervention. Overall, the data management will be in line with of the European General Data Protection Regulation.

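### Harms during the 12-week programme have a described recording channel only in the MultiMove arm, so they cannot be fairly compared with control

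*Protocol article*

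**What the plan says.** Two routes for detecting harms are described in the protocol article, Additional measurements. The first is not restricted by arm: "The participants will receive a medical check-up at the end of the study period at the same orthopaedic department" that carried out the initial check-up. Its stated purpose is to pick up beneficial and adverse events connected with the study intervention. The second is for everything else: "Any other harms, occurring during the study intervention, will be protocolled by the accredited instructors".

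Study interventions shows whom the instructors meet. "The sessions will be supervised by two accredited instructors and will be conducted with a maximum of 15 participants". "Additionally, the participants of the IG will receive MultiMove twice a week on non-consecutive days over a period of 12 weeks". For controls, "The participants of the CG will be examined in the same time period as the IG receiving only the standard therapy", "with the possibility to attend MultiMove as well, but not before the follow-up data collection is completed".

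On oversight, Data analysis and management says that "no data monitoring committee and interim analysis will be established, because of the minimal risks associated with the intervention".

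**The concern.** The recording rule follows allocation. An intervention participant who falls, strains something or has a pain flare in weeks 1 to 12 may come to an instructor's notice and be written down. A control with the same event in the same weeks has no described route until the check-up, and that check-up is framed around an intervention the control has not had. If the two routes are added together and tabulated by arm, part of any difference will reflect how closely each arm was watched.

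This matters for how the results are used. Participants are aged 50 or over and have degenerative lumbar disease. The Background says that motor-cognitive deficits in these patients may raise fall risk, and the Discussion plans later stages in inpatient rehabilitation and prevention. Harms data from this trial would naturally inform those stages.

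**Working it through.** The article states no adverse-event rate and no harms target, so there is no figure of the plan's own to reproduce. The sample size does not enter into this point. The check sets the described channels side by side.

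| Channel (section of the article) | MultiMove arm | Control arm |
|---|---|---|
| Instructor recording during the programme (Additional measurements; Study interventions) | Yes, at up to 2 × 12 = 24 classes | None; no class access before follow-up is complete |
| Telephone call after two consecutive missed sessions (Study interventions) | Yes | Not applicable |
| Reasons for stopping MultiMove early (Study interventions) | Yes | Not applicable |
| Check-up at the end of the study (Additional measurements) | Yes, once | Yes, once, but worded for intervention-related events |
| Harms item at the post (t1) and follow-up (t2) visits (Table 3; Study procedure) | None listed | None listed |

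At the requested 80% attendance, the 24 classes become 0.80 × 24 = 19.2. These are contacts at which an event could be recorded. The article does not say that instructors ask about harms at each one.

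The check-up is not dated beyond being at the end of the study period. Follow-up is at weeks 24–26, so the natural reading puts it 24 − 12 = 12 weeks or more after the last class. That is an inference.

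**Illustration; all detection rates are assumed.** Suppose true risk p is the same in both arms, the check-up detects a proportion c of events equally in both arms, and instructors independently detect a proportion i in the MultiMove arm.

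- Observed risk, control: p × c
- Observed risk, MultiMove: p × [1 − (1 − c)(1 − i)]
- Apparent risk ratio: [1 − (1 − c)(1 − i)] / c, which does not depend on p

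Expected counts use p = 0.20 and 50 per arm (100 randomised 1:1):

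| c | i | MultiMove events | Control events | Apparent ratio |
|---|---|---|---|---|
| 0.3 | 0.5 | 6.5 | 3.0 | 2.17 |
| 0.3 | 0.8 | 8.6 | 3.0 | 2.87 |
| 0.6 | 0.5 | 8.0 | 6.0 | 1.33 |
| 0.6 | 0.8 | 9.2 | 6.0 | 1.53 |
| 0.9 | 0.5 | 9.5 | 9.0 | 1.06 |
| 0.9 | 0.8 | 9.8 | 9.0 | 1.09 |

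For example, with c = 0.3 and i = 0.8: 1 − 0.7 × 0.2 = 0.86, and 0.86 / 0.3 = 2.87. The ratio tends to 1 as i falls towards 0, for instance if instructors see few of the events because most happen outside class. It rises further if the check-up's wording makes it less sensitive in controls. Counts from the check-up alone would not carry this imbalance, provided it is applied identically in both arms.

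**The case against.** Several points on the other side are sound and limit the finding.

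- **No harms comparison is planned.** Harms are not among the objectives or in Table 3, and no between-arm test is described. Instructor logging can be read as intervention-specific safety recording. This stands: the bias arises only if the arms are set against each other or pooled counts are reported.
- **A reader might infer that harms cannot be compared at all.** The article does not support that. The check-up is open to both arms, and events found there could be compared in principle.
- **A reader might set 25 recording occasions (24 classes plus the check-up) against 1, or conclude that the harm rate is falsely doubled.** The first treats every class as an enquiry, which the article does not say. The second depends on detection rates found nowhere in the documents.
- **A reader might infer that worsening pain in controls goes unseen.** It does not. Pain intensity and the Oswestry Disability Index are measured in both arms at all three time points, so lasting deterioration is captured equally. These measures do not record falls, injuries or short-lived events.
- **A reader might infer that the rule hides harm from MultiMove, or undermines the decision to have no monitoring committee.** Extra recording in one arm makes that arm look worse, and the low-risk statement is a prior judgement about oversight that the trial does not set out to test.
- **The full protocol may contain adverse-event forms for both arms.** It may, so the absence of a harms item from Table 3 is not itself the finding. The finding rests on a rule the article does state, which is one-sided as written.

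**Conclusion.** The concern holds in a limited form. As published, the recording of in-programme harms is confined to the MultiMove arm, and the one shared source is a single late check-up whose wording fits only that arm. Pooled counts would tend to lean against MultiMove under equal true risk, and in-programme harms cannot be fairly compared between arms. The direction follows from the text; the amount does not, and the tabulated ratios only show that it could be trivial or large depending on assumed detection. The conclusion assumes that the article's description is complete as to who records harms during the programme. The efficacy outcomes and the sample size are untouched. It is worth correcting because the repair is small and the harms data would otherwise be hard to interpret.

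**What to change.** 1. At the existing t1 and t2 visits, give both arms the same short self-completed adverse-event form covering all events since the last visit, whatever their presumed cause.
2. Word the form without reference to classes and keep it from the outcome assessors, for example by having it completed after the performance tests and handed in sealed. Study design and setting says all investigators are blinded, and an open conversation about events could reveal allocation at the visit where the Timed Up-and-Go is measured.
3. Reword the end-of-study check-up so that it covers all adverse events in both arms.
4. Base any between-arm harms summary on these shared sources only. Report instructor-recorded events, and anything learned in the calls after missed sessions, separately as intervention-arm data, since controls have no counterpart to either.

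Cost: a few minutes on a visit that already takes about 2.5 hours, more minor events on record, and a small residual unblinding risk that the sealed form limits.
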